### Study setting

In Canada, provincial governments have the primary responsibility for delivering healthcare services, with the result that healthcare systems and services differ across the 10 provinces. This means that assessing scale-up on a Canada-wide basis requires testing the intervention in more than one province. The trial will be conducted in two sites in each of three Canadian provinces, Ontario, Quebec and Prince Edward Island. These provinces were chosen because their provincial governments have strategic priorities related to health care services targeting: older adults, individuals with chronic conditions, and individuals who are high users of the health care system. The provinces, and the sites within them, were also chosen to capture: (a) different geographic settings (urban and rural), (b) a growing older adult population, (c) people of diverse socio-demographic and cultural backgrounds (e.g., English and French speaking, highly culturally diverse urban settings), and (d) providers demonstrating strong support for the intervention and having staff to support its implementation.

Each site will involve a primary care setting or diabetes education program (i.e., outpatient service that promotes health and supports lifestyle changes for people with diabetes or pre-diabetes) and a community partner site (e.g., Young Men’s Christian Association [YMCA]). The community partners were selected based on proximity to the primary care setting or diabetes education program and availability of staff members to participate in delivery of the intervention (e.g., a program coordinator for the group wellness sessions).

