#### Randomization design

Randomization procedures will be carried out as described in our previous protocol paper [46]. Briefly, the procedures include random assignment to the groups using a 1:1 allocation ratio, stratified permuted block randomization with the sequence generated by a biostatistician not involved in the recruitment process and with the study sites used as strata, and sequences entered into a centralized web-based randomization service (REDCap Version 11.1.9).

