#### Analysis: effectiveness evaluation (older adult and caregiver participants)

The baseline demographic and clinical characteristics of participants who completed both the baseline and 6-month assessments will be compared. Descriptive statistical analysis will be used to summarize outcome variables at baseline and 6 months. For continuous variables, means and standard deviations will be calculated, and for categorical variables, frequencies and proportions will be assessed. Analysis of covariance (ANCOVA) will be used to test the differences in outcome variables between the intervention and control group at 6 months. Separate ANCOVA models will be run for each primary and secondary outcome, with the 6-month change in the outcome as the dependent variable, group (intervention, control) as the independent variable, and the baseline value of the outcome as the covariate.

Statistical tests will use a 0.05 two-tailed level of significance and 95% confidence levels. An intention-to-treat (ITT) approach unadjusted for baseline characteristics will represent the primary analysis, using multiple imputation for missing data. Costs will be applied to the health and social service use reported by clients and caregivers. Group differences in the 6-month change in service use costs will be examined using parametric or non-parametric methods, depending on the distributional properties of the cost data [83].

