Sensitivity analyses will be conducted to test the robustness of the results for the primary outcome to various assumptions and analytical approaches used in the primary analyses [84]. A complete case analysis will be conducted to provide a comparison to the ITT results obtained using multiple imputation. A multivariable analysis that adjusts for residual baseline imbalances will be conducted to assess their impact on the effect estimates, if significant imbalances between groups exist post-randomization [85]. As a multi-site RCT, there exists the possibility that participants within a site may be more homogeneous compared to those from another site, thus a sensitivity analysis will be conducted that includes site as a covariate. Distributional assumptions underlying the ANCOVA model will be tested, with non-parametric methods explored if significant violations are present [86]. Since some participants in the intervention group were not offered the full intervention or did not receive any of the intervention (e.g., resulting from choice, due to COVID-related issues), we will conduct an analysis that excludes participants in the intervention group that did not receive any of the intervention for comparison with the results from the primary analysis (which include participants irrespective of whether they received the intervention or not). Finally, exploratory subgroup “sensitivity” analyses will be conducted to assess the potential benefit of the intervention for clinically-meaningful subgroups. The guidance from the recently-published Instrument for assessing the Credibility of Effect Modification Analyses (ICEMAN) [87] was reviewed in an effort to maximize the credibility of the subgroup analysis (if undertaken). The following three factors were pre-selected for the subgroup analysis: sex, number of chronic conditions, and province. We hypothesize that the intervention will be more effective in men because they typically engage in fewer self-management activities and access health care services less frequently than women [88]. We expect the intervention will be less effective in those with a higher number of chronic conditions because of the likelihood that they would have more complex care needs. We also expect to see variation in intervention effects across provinces due to contextual differences (e.g., health care systems, culture, rurality). Regression using two-way interactions between the study group (intervention versus control) and each characteristic will be conducted to determine subgroup effects [89, 90]. It is important to note that the subgroup “sensitivity” analyses will be regarded as exploratory, given the potential for the overall type I error to be inflated [86].

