#### Study setting

The trial had to be completely stopped at one of the Quebec sites due to the re-deployment of members of the intervention team to deal with COVID-19 issues. The research team from Prince Edward Island has agreed to recruit an additional 44 participants and provide the intervention virtually by videoconference or by telephone, based on the participant’s preferences, using the same RA, RC and intervention team. Although this reduces the diversity of our sample due to a smaller representation from the province of Quebec, it allows us to preserve the overall sample size of the study.

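### Randomisation is stratified by site, but the primary ANCOVA leaves site out and uses it only in a sensitivity analysis, which makes the primary test slightly conservative

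*Protocol article*

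**What the plan says.** Under Randomization design, the protocol article specifies "random assignment to the groups using a 1:1 allocation ratio, stratified permuted block randomization", "with the study sites used as strata". The Study setting section plans six such sites: "The trial will be conducted in two sites in each of three Canadian provinces, Ontario, Quebec and Prince Edward Island". Among the COVID-19 modifications it reports that "The trial had to be completely stopped at one of the Quebec sites", with 44 further participants to be recruited in Prince Edward Island.

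The section on the analysis of effectiveness for older adults and caregivers sets the model terms. The dependent variable is the 6-month change, with "group (intervention, control) as the independent variable, and the baseline value of the outcome as the covariate". It also states: "An intention-to-treat (ITT) approach unadjusted for baseline characteristics will represent the primary analysis, using multiple imputation for missing data". Site appears only among the sensitivity analyses for the primary outcome. The reason given is that "there exists the possibility that participants within a site may be more homogeneous compared to those from another site", and the sentence ends "thus a sensitivity analysis will be conducted that includes site as a covariate".

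The article therefore names the terms of the primary model and gives the stratification factor a secondary role. This is a stated choice, not a detail left open for an analysis plan.

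**The concern.** Blocking within site forces the arms to be nearly equal in size at every site. Differences between sites in the level of the outcome then largely cancel out of the treatment contrast. A model without a site term does not know this. It counts those differences as residual noise and reports a standard error larger than the real sampling error of the estimate. The precision that stratification provides is not used where it matters, in the primary confidence interval and test.

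The article treats site as a robustness question about similarity within sites. With individual randomisation inside each site, that similarity does not threaten validity. It is a source of precision that the primary model can use. There is also a practical risk: if the two planned models fall on opposite sides of 0.05, the one that reflects the randomisation would be the secondary one.

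**Working it through.** **Inputs from the article.** Mean difference 3.68, SD 9.68, two-sided alpha 0.05, 80% power, 20% attrition, total 264, 44 per site (Sample size); six sites (Study setting).

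**Assumed, because the article does not give it.** The share ρ of the residual variance, after baseline MCS, that lies between sites: 0, 2%, 5% or 10%. The 9.68 is used as the residual SD.

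**The article's own figure.** Standardised effect 3.68/9.68 = 0.380. A two-sample t-test at 80% power needs 109.6, so 110 per arm or 220 in total, and 220 × 1.2 = 264. The stated total reproduces. With 20% loss, 264 × 0.8 ≈ 211 are analysed.

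**Closed form, taking exact balance within site.**
- Reported SE without site: 9.68 × √(4/211) = 1.333
- True SE, which is also the SE with site in the model: 1.333 × √(1 − ρ)
- True type I error without site: 2 × [1 − Φ(1.96/√(1 − ρ))]
- Power without site: Φ((3.68 − 1.96 × 1.333)/true SE)
- Power with site: Φ(3.68/true SE − 1.96)

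| Assumed ρ | SE without site | SE with site | Overstated by | Type I error without site | Power without site | Power with site |
|---|---|---|---|---|---|---|
| 0 | 1.333 | 1.333 | 0 | 0.050 | 78.8% | 78.8% |
| 2% | 1.333 | 1.319 | 1.0% | 0.048 | 79.1% | 79.6% |
| 5% | 1.333 | 1.299 | 2.6% | 0.044 | 79.4% | 80.9% |
| 10% | 1.333 | 1.264 | 5.4% | 0.039 | 80.1% | 82.9% |

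**Allowing for attrition.** Loss to follow-up partly breaks the balance within site, so the closed form is an upper bound on the effect. Simulations with six sites of 44, blocks of 4 (the article states no block size) and random 20% loss gave the following.

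| Assumed ρ | Type I error without site | Power gained by adding site |
|---|---|---|
| 2% | about 0.046 | about 0.2 points |
| 5% | about 0.044 | about 1.1 points |
| 10% | about 0.041 | about 2.3 points |

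At a share of zero there was no gain or loss. A repeat with 20,000 runs per setting gave 0.047, 0.046 and 0.041, with gains of about 0.3, 1.0 and 2.5 points.

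A further simulation included a baseline covariate, used 35 or 36 analysed per site and had 8,000 runs. At 10% it gave power of 79.0% without site and 82.2% with it, a gain of 3.2 points, and null rejection of 4.4% and 5.5%. The Monte Carlo standard error of a 5% rate at that size is √(0.05 × 0.95/8000) ≈ 0.24 points, so these rates are less exact. At zero share it gave power of 78.6% without site and 78.3% with it.

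Taken together, about 2.5 points is a fair figure for the 10% end of the range.

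**The case against.** The best defence is that little is at stake. The model with arm and baseline value estimates the treatment effect without bias, its error is on the cautious side, and the site-adjusted result for the primary outcome is already promised. Only the labels of two planned models are in question. All of that is true, and it limits the weight of the point. It does not justify the present order, because the adjusted model follows the randomisation and costs almost nothing even if sites do not differ.

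The size also rests on an assumed variance share. The article calls similarity within sites a possibility and gives no estimate, so a share of zero cannot be excluded.

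A reader might infer more from other parts of the article, without support:
- **Provincial differences.** The differences in health system, culture and rurality are offered as reasons why the intervention effect may vary. That is effect modification, for which an interaction by province is planned. It does not show that outcome levels differ between sites.
- **Delivery format.** This concerns what the intervention arm received, and a separate subgroup analysis is planned for it.
- **Power.** About 78.5% by t-test at 211 analysed, against the stated 80%, follows from how attrition was added to the sample size. It is a separate matter, and the figure gives no credit for the baseline covariate.
- **The 44 added participants.** Nothing says they formed their own randomisation stratum. The article names sites as strata and says the added recruitment uses the same research and intervention staff.

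**Conclusion.** The point holds as a modest flaw in a stated analysis choice: the primary ANCOVA omits the factor used to stratify the randomisation. Under an assumed between-site share of 0 to 10% of residual variance, type I error falls from about 0.05 to about 0.04, and about 0 to 2.5 points of power are given up. These figures assume 211 analysed, a residual SD of 9.68, six sites, blocks of 4 and loss at random.

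A reader used to cluster trials might infer that ignoring site makes the standard error too small and inflates false positives, or that the effect estimate is biased. The design does not support either reading. Individuals are randomised 1:1 within site, so the error runs towards intervals that are too wide. A significant primary result would not be undermined by this point; what is lost is some chance of detecting a real effect.

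**What to change.** Restate the primary analysis as: 6-month change in MCS on arm, baseline MCS and randomisation site as a fixed effect, with the site levels matching the strata actually used in the randomisation. Use the same terms for the other older-adult outcomes analysed by ANCOVA. Costs can stay outside this, since the article allows non-parametric methods for them. Report the model without site as the sensitivity analysis, and settle the order before allocation is unblinded.

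The cost is a change of wording and about five degrees of freedom (6 sites − 1). With about 211 analysed, residual degrees of freedom go from 211 − 3 = 208 to 211 − 8 = 203. No new data are needed.

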#### Overview of pandemic impact, importance and key decisions

The trial was underway at all sites at the time that the COVID-19 pandemic hit Canada (March 2020). As noted in the CONSERVE guidelines, the impact of the pandemic on studies already underway “is an exemplar” of extenuating circumstances that are unavoidable and beyond the control of the investigators, funding agencies, and trial sites [58]. In our study, the pandemic resulted in a range of impacts at the sites, including delays in the implementation of the intervention, discontinuation of the intervention, and shifting from in-person to virtual delivery of the intervention and data collection methods. These impacts in turn triggered important modifications to the study protocol that had implications for the study feasibility, intervention implementation, intervention effectiveness, and analytical methods in the trial. The research team planned, reviewed and achieved consensus on the mitigation strategies proposed to address the pandemic impacts.

The pandemic resulted in stopping the study at all sites on March 16, 2020. The next steps at each site were dependent on the stage of the study at the site, with the result being the offering of different doses and/or delivery formats for the intervention to participants within and across sites. We moved to virtual approaches to deliver the intervention and to collect data at all sites, which required obtaining ethics approvals at the sites. One site had the intervention team re-deployed to deal with COVID-19 issues and the intervention could not be restarted. The details of these and other impacts and the mitigation strategy to address them are outlined below for the SPIRIT checklist items that were affected.

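### The planned analysis that drops never-treated participants from the intervention arm alone is not a randomised comparison and cannot test whether the ITT result is robust

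*Protocol article*

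**What the plan says.** All of this is in the protocol article, mainly in the section on analysis of the effectiveness evaluation.

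- Primary analysis: "An intention-to-treat (ITT) approach unadjusted for baseline characteristics will represent the primary analysis, using multiple imputation for missing data". The ANCOVA model has group as the independent variable and "the baseline value of the outcome as the covariate".
- Purpose of the further analyses: "Sensitivity analyses will be conducted to test the robustness of the results for the primary outcome".
- The analysis at issue: "we will conduct an analysis that excludes participants in the intervention group that did not receive any of the intervention", offered "for comparison with the results from the primary analysis (which include participants irrespective of whether they received the intervention or not").
- Reasons for exclusion: the people concerned "did not receive any of the intervention (e.g., resulting from choice, due to COVID-related issues").
- Allocation, under Randomization design: "random assignment to the groups using a 1:1 allocation ratio, stratified permuted block randomization", with study sites as strata.

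The exclusion rule names only the intervention group. That all controls stay in is an inference from that wording, but the natural one. The article labels its subgroup analyses exploratory, both here and in the COVID-19 section on statistical methods. The exclusion analysis carries no such label, no caution about selection and no stated adjustment for predictors of receipt.

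**The concern.** Whether an intervention participant receives anything is known only after randomisation and only in that arm. The control arm contains a similar share of people who would have received nothing if assigned to the programme, but nobody can tell who they are. Removing such people from one side leaves a selected group compared with an unselected one. Because choice is a stated reason for non-receipt, a link with prognosis is plausible in this population, and adjusting for baseline MCS alone cannot be relied on to remove it.

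The analysis also answers a different question. ITT estimates the effect of being assigned, whereas the exclusion aims at the effect in those who received something. The two can differ with no fault in either, so the comparison does not serve its stated purpose. What is at stake is how the primary result is read and supported, not the primary result itself.

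**Working it through.** **Inputs from the protocol article (Sample size):** mean difference 3.68, SD 9.68, 80% power, two-sided alpha 0.05, 20% attrition, total 264.

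**The plan's own figure.** A two-sample t-test with these inputs needs 109.6, so 110 per arm. 110 × 1.2 = 132 per arm, and 2 × 132 = 264, as stated. No figure is given for the exclusion analysis, so 264 serves only to set the scale.

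**Assumed inputs, not in the documents.** p is the share who receive nothing if assigned to the intervention (the same in both arms on average, by randomisation). g is the number of MCS points by which such people's 6-month change is worse, whichever arm they are in, after any adjustment for baseline. Ranges used: p 10–30%, g 2–5. Write δ for the effect in receivers and μ for the untreated mean change of would-be receivers.

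**Expected values**

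- Intervention arm after exclusion: μ + δ
- Control arm, all kept: μ − p·g
- Exclusion analysis: δ + p·g, so the bias for the effect in receivers is **p·g**
- ITT: (1 − p)·δ
- Complier average effect, ITT/(1 − p): δ

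**Bias in MCS points, with simulated two-sided rejection when the true effect is zero** (132 per arm, SD 9.68, 4,000 runs per cell)

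| p | g = 2 | g = 3.68 | g = 5 |
|---|---|---|---|
| 10% | 0.20 (5.0%) | 0.37 (6.1%) | 0.50 (6.9%) |
| 20% | 0.40 (6.4%) | 0.74 (8.7%) | 1.00 (11.7%) |
| 30% | 0.60 (7.2%) | 1.10 (13.3%) | 1.50 (20.2%) |

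Against the planned difference, 0.20/3.68 = 5% and 1.50/3.68 = 41%. With g = 0 the bias is zero and rejection stays at about 5%. With g negative the signs reverse. In the same runs ITT and the complier average estimate stayed centred on zero.

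**With a true effect of 3.68 in receivers, p = 20%, g = 5:** the simulated means were 4.68 for the exclusion analysis, 2.94 for ITT and 3.68 for the complier average estimate. The formulas give 3.68 + 0.20 × 5 = 4.68 and 0.80 × 3.68 = 2.94.

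**Why the comparison with ITT is uninformative.** The expected gap is (δ + p·g) − (1 − p)·δ = p·(δ + g).

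- With no selection at all (g = 0), p = 20% and δ = 3.68, the gap is still 0.20 × 3.68 = 0.74, although ITT is sound.
- The gap vanishes when g = −δ, so close agreement can hide selection that offsets a real effect.

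One observed gap cannot separate δ from g.

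**The case against.** **Limited role.** The primary analysis is ITT with multiple imputation, and no decision rule rests on the exclusion. This stands, and it limits the importance of the point.

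**Size and direction are assumed.** This also stands. A reader might infer that the analysis will overstate benefit. The documents do not support that: people who decline by choice may be healthier and see less need, COVID-related non-receipt may be unrelated to individual prognosis, and baseline adjustment absorbs part of any difference.

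**A whole stopped site.** A reader might infer that one Quebec site's intervention participants would be dropped while its controls stay, upsetting the stratification. The article says only that at that site "the intervention could not be restarted", which suggests it had started. It also says that participants at all sites will be offered at least one visit and one group session. Whether anyone randomised there received nothing, or enters the analysis, is not stated, so the point does not rest on this.

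**Use in scale-up.** A reader might also infer that this is the only analysis by receipt, or that it would serve as confirmatory evidence for scale-up. Neither is supported. The COVID-19 section on statistical methods also plans comparisons by in-person versus virtual delivery, and the scalability sections cite effectiveness results generally without mentioning this analysis.

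**Precision.** The complier average estimate is not clearly better on total error. Take 264 × 0.8 ≈ 211 analysed, 105.5 per arm, SD 9.68:

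- p = 20%, g = 4: the exclusion has SE 9.68 × √(1/84.4 + 1/105.5) = 1.41 and bias 0.8, so root mean square error √(1.41² + 0.8²) = 1.62. The complier average SE is 9.68 × √(2/105.5)/0.8 = 1.67.
- p = 10%, g = 2: 1.38 against 1.48.

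This stands. The reason to prefer the complier average effect is that it has a defined target and rests on randomisation, not that it is more precise.

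**Conclusion.** The point holds as a cheap and worthwhile correction to one sensitivity analysis. The one-arm exclusion is stated in the protocol article, depends on a post-randomisation event partly driven by choice, and cannot be matched in the control arm. It therefore breaks the randomised comparison and changes the effect being estimated. Its agreement or disagreement with ITT is not evidence about robustness.

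The mechanism is certain; the size is not. Under assumed p of 10–30% and g of 2–5 MCS points the bias is about 0.2 to 1.5 points (5% to 41% of 3.68), with direction set by the sign of g and no bias if g = 0. The primary ITT analysis is untouched.

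**What to change.** Estimate the effect among receivers as a complier average causal effect:

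- Method: two-stage least squares with randomised arm as the instrument.
- Exposure: receipt of any visit (home, telephone or virtual) or any group session. The adoption measure in Table 2 requires at least one of each; using it would count partial receivers as unexposed.
- Covariates: baseline MCS and site.
- Population: all randomised participants, with the same multiple imputation as the primary analysis.

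State the two assumptions. First, assignment alone has no effect on people who receive no visit or session. This needs a sentence of defence, because care coordination, case conferences and alerts to physicians are also part of the programme. Second, controls have no access. The rule that intervention-team members do not deliver usual care to controls supports this.

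If the one-arm exclusion is also kept, label it exploratory and non-randomised, adjust it for site and baseline predictors of receipt, and do not present it as a robustness check on ITT.

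Cost: plan wording and a few lines of code. The visit and group-session records listed in Table 3 already supply the receipt data. The interval is wider than the ITT interval by about 1/uptake: 1.11 times at 90% uptake, 1.25 at 80% and 1.43 at 70%.
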